## Abstract

**Question:**

Can tropisetron reduce the risk of emergence delirium in patients after noncardiac surgery?

**Findings:**

This trial protocol describes a randomized clinical trial of an estimated 1508 patients undergoing noncardiac surgery. The primary outcome is incidence of emergence delirium.

**Meaning:**

This ongoing clinical trial will supply evidence of the effectiveness of preoperative tropisetron treatment to reduce occurrence of emergence delirium.

## Introduction

In patients undergoing anesthesia and surgery, approximately 11% to 51% will have postoperative delirium,^1^ which is characterized by cognitive decline, inattention, and a change in level of consciousness.^2^ It is a common neuropsychiatric complication of surgery, especially in elderly patients.^3^ Patients could present with delirium early in the postanesthesia care unit (PACU),^4,5,6^ with an incidence of 3.7% to 22.2%.^7,8,9^ The fluctuating mental status of delirium is associated with delayed postoperative recovery, longer hospital stay, and increased morbidity and mortality.^10,11,12^ Patients experiencing postoperative delirium are more likely to develop permanent cognitive disturbances.^13,14^ Thus, pharmacological prevention is needed to lower the risk of postoperative delirium and improve prognosis of patients.

Tropisetron is a serotonin (5-hydroxy-tryptamine) 3 receptor antagonist and is frequently used in prevention and treatment of postoperative nausea and vomiting.^15,16^ In addition, this drug is also a high-affinity partial agonist of α7 nicotinic acetylcholine receptors (α7-nAChRs).^17,18,19^ Triggering α7-nAChRs has demonstrated neuroprotective effects in various cognitive deficiency diseases.^20^ Most recently, beneficial effects in cognitive function, such as memory performance, have been reported of tropisetron in animals.^17,21^ In mouse models of Alzheimer disease, tropisetron induced greater improvements in spatial and working memory.^22^ The mechanism involves an increase in the ratio of α-secretase amyloid precursor protein to amyloid β_1-42_^18,22^ and protection against amyloid β-induced neurotoxicity.^23^ In a randomized double-blind study, patients with schizophrenia who received tropisetron were found to have overall improvement of cognitive deficits compared with patients who received a placebo.^24^ In perioperative settings, only a published hypothesis is available, showing that tropisetron could act as potential therapeutic drug for postoperative cognitive dysfunction, considering the shared identical mechanisms between postoperative cognitive dysfunction and Alzheimer disease.^25^ Taken together, evidence suggests that tropisetron is a promising approach in preventing delirium. However, no large clinical trials have studied the effect of tropisetron on emergence delirium. The aims of this study are (1) to determine the effect of tropisetron on the incidence of emergence delirium and (2) to better understand beneficial effects of tropisetron on the incidence of postoperative delirium and other delirium-related outcome measures compared with placebo.

## Methods

### Trial Status

The study is currently recruiting patients. Recruitment began August 1, 2019. We expect the study to be complete in December 2021. The trial protocol is available in the Supplement.

### Study Design and Setting

The study is being conducted in Beijing Chaoyang hospital affiliated with Capital Medical University, Beijing, China. The trial has been approved by the Medical Ethics Committee of the Chaoyang Hospital, Beijing. This study protocol is strictly in accordance with the Standard Protocol Items: Recommendations for Interventional Trials (SPIRIT) reporting guideline.^26,27^

The study is a double-blinded, randomized placebo-controlled trial that includes 1508 patients undergoing noncardiac surgery. Potential participants undergoing noncardiac surgery will be screened for eligibility criteria. All enrolled patients will be randomly divided into either the tropisetron group or placebo group at a 1:1 ratio. The primary end point is the incidence of emergence delirium.

### Eligibility Criteria

Inclusion criteria in the study are (1) 18 years or older; (2) general anesthesia for elective noncardiac surgery; (3) American Society of Anesthesiologists physical status score I to III; and (4) signed informed consent. Exclusion criteria are (1) history of neurological disease (eg, dementia or Parkinson disease); (2) neurosurgery; (3) history of psychiatric disease (eg, schizophrenia); (4) treatment with antipsychotic drugs during the last 30 days before enrollment; (5) unable to complete neuropsychological tests, including patients with severe visual or hearing impairment; (6) a Montreal Cognitive Assessment score of less than 10; (7) severe intraoperative adverse events (eg, cardiac arrest); and (8) contraindication to tropisetron.

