### Recruitment and Consent

Participants are recruited in the hospital ward 1 day before surgery. Team members visit patients who meet the eligibility criteria and invite them to join the study. All participants sign the informed consent form before enrollment in this trial.

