### Intervention and Control

After randomization, patients enrolled in this trial come to the operating room and undergo standard monitoring, including electrocardiography, blood pressure, and oxygen saturation. Intravenous access is then established. The intervention group receives a 5-mg dosage of tropisetron as a bolus intravenously once before induction of anesthesia, whereas the control group receives placebo of 0.9% saline solution. Patients in both groups receive general anesthesia and tracheal intubation. Mean artery blood pressure is maintained above 65 mm Hg during surgery, and the bispectral value is maintained at 40 to 60. Electroencephalographic data are acquired by the bispectral monitoring system for the entire duration of the operation. Information is collected on surgical and anesthesia techniques used (eg, intraoperative medication, anesthesia methods, type of surgery, laparoscopic or open procedure, duration of surgery, estimated blood loss during surgery, intraoperative infusion, blood transfusion during surgery, and patient-controlled analgesia). Patients are transferred to the PACU after surgery. Patients in both groups receive nondrug interventions in the postoperative period. The Enhanced Recovery After Surgery pathway is not applied in our study.

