### Outcomes

The primary outcome in this study is the incidence of emergence delirium within 1 hour after tracheal extubation measured using the validated Chinese version of the CAM-ICU.^36^ The CAM-ICU was validated against the *Diagnostic and Statistical Manual of Mental Disorders* (Fifth Edition) criteria for delirium in PACU settings based on the guideline.^38^ With a specificity of 98% and low sensitivity, we may detect the positive delirium cases conservatively in this study.^39^ The positive CAM-ICU test result requires the presence of (1) acute changes in mental status with a fluctuating course and (2) inattention, with either (3) disorganized thinking or (4) altered level of consciousness. Patients with delirium may display hyperactive or hypoactive signs. Hyperactive delirium is defined as RASS scores from 1 to 4, and hypoactive delirium is defined as RASS scores from −3 to 0.^40^ Secondary outcomes include (1) incidence of postoperative delirium within 3 days after surgery (defined as positive CAM-ICU test result); (2) nausea and vomiting within 3 days after surgery; (3) postoperative pain intensity at PACU discharge and 24, 48, and 72 hours after surgery, measured using the visual analog scale (scores range from 0-10, with higher scores indicating greater pain); (4) adverse events (cardiac arrhythmias, cardiogenic shock, and other unexpected adverse events) within 3 days after surgery; (5) length of hospital stay; and (6) all-cause mortality during hospitalization.

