### Statistical Analysis

The primary analysis will be according to the intention-to-treat principle and complemented with a per protocol analysis.^41^ Nonadherence refers to patients who fail to receive the intervention or placebo after randomization, owing to cancelled operation or refusing to participate on the day of surgery. To control bias from nonadherence, sensitivity analyses will be conducted excluding participants with nonadherence.

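### Exclusion criterion 7 rests on an intraoperative event, so it can act only on patients already randomised and dosed, which conflicts with the intention-to-treat analysis

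*Protocol article*

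**What the plan says.** All references are to the Protocol article.

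- **Eligibility Criteria.** Item 7 of the exclusion list reads "7) severe intraoperative adverse events (eg, cardiac arrest" (the bracket closes the item).
- **Recruitment and Consent.** "Participants are recruited in the hospital ward 1 day before surgery". The schedule Table marks eligibility screening, consent and randomisation all at Visit 1, on that day.
- **Intervention and Control.** "After randomization, patients enrolled in this trial come to the operating room", and then "The intervention group receives a 5-mg dosage of tropisetron as a bolus intravenously once before induction of anesthesia". The Table puts the intervention at Visit 2 and the anaesthesia period at Visit 3.
- **Statistical Analysis.** "The primary analysis will be according to the intention-to-treat principle and complemented with a per protocol analysis". The one group singled out for exclusion is the non-adherent, and only in sensitivity analyses: "Nonadherence refers to patients who fail to receive the intervention or placebo after randomization", because the operation was cancelled or the patient declined on the day.
- **Outcomes.** Secondary outcome 4 is "adverse events (cardiac arrhythmias, cardiogenic shock, and other unexpected adverse events) within 3 days after surgery". Secondary outcome 6 is death from any cause in hospital. In the Table the adverse event row is blank at Visit 3 and is marked from the PACU to postoperative day 3.
- **Safety and Adverse Event Reporting.** Serious events, among them death and life-threatening events, will be reported. An independent board oversees the trial, with safety analyses after 500 and 1000 participants.

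**The concern.** An eligibility criterion should be decidable before allocation. This one is not, because it depends on what happens during the operation. Its only possible effect is to take out patients who have been allocated and, on the stated sequence, injected.

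Two things are at stake. The first is the primary analysis set: an intention-to-treat analysis keeps randomised patients whatever happens to them later, and item 7 says otherwise for one group. The second is safety. Cardiac arrest is of the same kind as the cardiac events named in secondary outcome 4, and an intraoperative death falls within in-hospital mortality. If these patients are dropped, the comparison by arm loses events that the study drug could in principle influence. The schedule adds to this, since adverse events are not marked for collection during anaesthesia.

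**Working it through.** **Order of events**

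| Step | When | Source |
|---|---|---|
| Screening, consent, randomisation | 1 day before surgery (Visit 1) | Table; Recruitment and Consent |
| Study drug or placebo | Before induction (Visit 2) | Table; Intervention and Control |
| Event named in item 7 | During the operation (Visit 3) | Eligibility Criteria |
| First scheduled adverse event collection | PACU (Visit 4) | Table |

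Item 7 can be met only at the third step, after allocation and dosing. A dosed patient with an intraoperative cardiac arrest is not non-adherent under the article's definition, which covers only patients who never received study drug. The analysis section therefore gives no ground for leaving this patient out, while the eligibility section excludes the patient. The article does not say which prevails.

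**Number of patients.** There is no figure in the plan to reproduce, because no rate of severe intraoperative events is given. Assume 0.3% to 1%:

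- 1508 × 0.003 = 4.5, about 5 patients
- 1508 × 0.01 = 15.1, about 15 patients

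**Effect on power.** Inputs from Sample Size Calculation: 15% in controls, a 6% reduction read as absolute (so 9%), 640 per group, α = 0.05. The standard two-proportion calculation at n = 640 × (1 − x), where x is the proportion excluded, gives:

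| x | One-sided power | Two-sided power |
|---|---|---|
| 0 | 95.2% | 91.1% |
| 1% | 95.0% | 90.9% |
| 2% | 94.9% | 90.6% |

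These values exceed the planned 80%. That is a separate question about the sample size and does not bear on this point. The change from row to row is what matters here, and it is negligible.

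**Effect on the primary estimate.** Suppose a proportion *e* of an arm is excluded, the excluded patients have delirium risk *r*, and the arm's full risk is *p*. The observed risk is then

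(p − e·r) / (1 − e).

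Take no true effect, with p = 15% in both arms, and let *r* be the same in both arms. All *e* and *r* are assumptions. The shift is the placebo risk minus the tropisetron risk, in percentage points, so a positive value favours tropisetron.

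| Excluded, tropisetron vs placebo | r = 15% | r = 50% | r = 100% |
|---|---|---|---|
| 1% vs 1% | 0 | 0 | 0 |
| 1% vs 0.3% | 0 | 0.25 | 0.60 |
| 2% vs 1% | 0 | 0.36 | 0.88 |
| 3% vs 1% | 0 | 0.73 | 1.77 |

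Worked example for 1% vs 0.3% with r = 50%:

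- Placebo: (0.15 − 0.0015)/0.997 = 14.89%
- Tropisetron: (0.15 − 0.005)/0.99 = 14.65%
- Difference: 0.25 points before rounding of the two risks

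Reversing the arms reverses the sign. The last two rows lie above the assumed 0.3% to 1% and serve as a stress test. Within the assumed range the shift is at most 0.60 points, against a design difference of 6 points.

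**Effect on safety and mortality.** This cannot be computed. The article gives no mortality rate and nothing on how many deaths would fall in patients meeting item 7.

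**The case against.** The strongest reply is that removal from the analysis is implied, not stated. Item 7 sits in the eligibility list, the analysis section names intention-to-treat as primary, and the item may be a misplaced discontinuation rule or a per-protocol exclusion that the full protocol explains. This stands in part. A reader might infer that the plan breaks intention-to-treat outright, and the article does not go so far. It does state an exclusion that, if followed, gives the wrong analysis set. That is a conflict between two stated rules, not a detail left to another document.

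A reader might also infer that item 7 hides serious harms. The article does not support that: deaths and life-threatening events are to be reported and an independent board reviews safety. What remains is a risk. The safety section does not say that patients excluded under item 7 stay in the comparisons by arm, and scheduled adverse event collection begins only in the PACU.

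Nor is this selection on the primary outcome. The event is a post-treatment event and, on the wording of secondary outcome 4, intraoperative events are not clearly inside even that outcome, because its window opens after surgery.

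Finally, anaesthesiologists and assessors are blinded, and some of these patients would have no PACU delirium assessment anyway. Blinding limits selective use of item 7, but it cannot prevent imbalance if the drug itself changes the event rate. Missing assessments are a reason to count the outcome as missing, not to drop the patient.

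**Conclusion.** The point holds on the article's own timeline. Item 7 cannot be assessed at enrolment. Applied as written, it excludes randomised, treated patients for a post-treatment event, contrary to the intention-to-treat primary analysis, and it risks leaving serious intraoperative events and deaths out of the safety and mortality comparisons.

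Its size is modest for the primary outcome: about 5 to 15 of 1508 patients if 0.3% to 1% is assumed, almost no loss of power, and a probably small shift in the estimate. Bias requires that exclusions, or the risk in those excluded, differ by arm; its direction cannot be known in advance.

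A reader might go on to infer that safety results would be biased towards no harm, or would lose most of their signal. The first would require that tropisetron raises the rate of such events. The second would require an overlap between excluded patients and deaths that the article does not give. Neither is established.

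**What to change.** 1. Delete item 7 from the exclusion criteria.
2. State that every randomised patient with a severe intraoperative event stays in the intention-to-treat, adverse event and in-hospital mortality analyses.
3. Extend adverse event recording in the Table to Visit 3, and open the window of secondary outcome 4 to include the operation, so that these events are reported by arm.
4. Record the primary outcome as missing when the PACU CAM-ICU cannot be obtained. Follow-up Visits already does this for patients who stay unarousable beyond one hour after extubation. The rule needs extending, since its clock starts at extubation and a patient with a severe event may not be extubated.
5. Restore patients already excluded under item 7 as far as their records allow.

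The cost is a short amendment that touches the eligibility list, the Table and the outcome definition, plus a few more missing primary outcomes. No extra patients are needed. For patients already excluded, PACU and ward assessments that were not done are lost; only what is in the medical record can be recovered. The article does not show whether such patients were followed.

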### Recruitment and Consent

Participants are recruited in the hospital ward 1 day before surgery. Team members visit patients who meet the eligibility criteria and invite them to join the study. All participants sign the informed consent form before enrollment in this trial.

### Randomization and Blinding

Participants are randomly assigned to the tropisetron group or the placebo group with a 1:1 ratio with a block size of 4 (SAS software, version 9.4 [SAS Institute, Inc]). A statistician who is not involved in data collection or analysis ([name]) produces the randomization list, which is printed out and sealed in an opaque envelope for each participant’s assignment. A study nurse ([name]) assigns the participants to treatment by telephoning a contact in Beijing Chaoyang hospital. The contact is not involved in the number generation and recruitment process. Participants are then randomly allocated to identical ampoules with 5 mg of tropisetron or 0.9% saline solution. The syringe with a total volume of 1 mL is given to anesthesiologists before entering the operating room. Both participants and anesthesiologists are blinded to randomization assignments. Unblinding is permissible if necessary for safety reasons.

### Intervention and Study Visits

#### Baseline Hospital Ward Visit

Baseline assessments are conducted in the hospital ward. Demographic information, medical history, health history (eg, long-term alcohol use and smoking status), hearing and vision measurement, baseline laboratory tests, and electrocardiography are collected from the electronic medical record. One day before surgery, patients undergo assessments, including pain measured by a visual analog scale,^28,29^ depression by the 9-item Patient Health Questionnaire,^30^ anxiety by the 7-item Generalized Anxiety Disorder Scale,^31^ insomnia by Insomnia Severity Index,^32^ and cognitive function by the Montreal Cognitive Assessment,^33^ with the aim of identifying risk factors of emergence delirium. All planned study visits are presented in the Table.

**Table. zoi200508t1:** The Schedule of Planned Investigation

Study component	Visit 1	Visit 2	Visit 3	Visit 4	Visit 5	Visit 6	Visit 7	Visit 8
Time	1 d before surgery	Before anesthesia	During anesthesia	PACU	POD 1	POD 2	POD 3	Hospital discharge
Eligibility screen	X	−	−	−	−	−	−	−
Informed consent	X	−	−	−	−	−	−	−
Demographic characteristics	X	−	−	−	−	−	−	−
Randomization	X	−	−	−	−	−	−	−
Intervention	−	X	−	−	−	−	−	−
MoCA	X	−	−	−	−	−	−	−
VAS	X	−	−	X	X	X	X	−
PHQ-9	X	−	−	−	−	−	X	−
GAD-7	X	−	−	−	−	−	X	−
ISI	X	−	−	−	−	−	X	−
EEG frequency spectrum	−	X	X	X	−	−	−	−
Blood draw for biomarkers	−	X	−	X	−	−	−	−
CAM-ICU	−	−	−	X	X	X	X	−
Nausea and vomiting	−	−	−	X	X	X	X	−
Adverse events	−	−	−	X	X	X	X	−
Hospital stay	−	−	−	−	−	−	−	X

Abbreviations: CAM-ICU, Confusion Assessment Method for the Intensive Care Unit; EEG, electroencephalography; GAD-7, 7-item Generalized Anxiety Disorder Scale; ISI, Insomnia Severity Index; MoCA, the Montreal Cognitive Assessment; PHQ-9, 9-item Patient Health Questionnaire; POD, postoperative day; VAS, visual analog scale; X, present; minus sign, absent.

#### Baseline Operating Room Visit

An electroencephalography (EEG) monitor (the bispectral index [BIS; Covidien]) is applied in participants in both groups during the preoperative period (5 minutes with eyes closed). A blood sample is drawn before intervention for identifying potential biomarkers, including interleukin 1β (IL-1β), IL-6, IL-8, IL-10, IL-12p70, IL-17A, IL-18, IL-23, interferon γ, monocyte chemoattractant protein 1, receptor for advanced glycation end products, tumor necrosis factor, C-reactive protein, tau, phosphorylated tau 231, amyloid β_1-42_, vascular endothelial growth factor D, ubiquitin C-terminal hydrolase ligase-1, brain-derived neurotrophic factor, α-synuclein, and serum amyloid A.

### Intervention and Control

After randomization, patients enrolled in this trial come to the operating room and undergo standard monitoring, including electrocardiography, blood pressure, and oxygen saturation. Intravenous access is then established. The intervention group receives a 5-mg dosage of tropisetron as a bolus intravenously once before induction of anesthesia, whereas the control group receives placebo of 0.9% saline solution. Patients in both groups receive general anesthesia and tracheal intubation. Mean artery blood pressure is maintained above 65 mm Hg during surgery, and the bispectral value is maintained at 40 to 60. Electroencephalographic data are acquired by the bispectral monitoring system for the entire duration of the operation. Information is collected on surgical and anesthesia techniques used (eg, intraoperative medication, anesthesia methods, type of surgery, laparoscopic or open procedure, duration of surgery, estimated blood loss during surgery, intraoperative infusion, blood transfusion during surgery, and patient-controlled analgesia). Patients are transferred to the PACU after surgery. Patients in both groups receive nondrug interventions in the postoperative period. The Enhanced Recovery After Surgery pathway is not applied in our study.

### Follow-up Visits

In the PACU, participants are screened using the Confusion Assessment Method for the Intensive Care Unit (CAM-ICU)^34,35,36^ at 15 and 30 minutes after tracheal extubation and at discharge from PACU (within 1 hour after tracheal extubation). Delirium is defined as a positive CAM-ICU test result at either of these 3 time points. The Richmond Agitation Sedation Scale (RASS) is performed before the CAM-ICU test to assess the depth of sedation.^37^ If the RASS score is −4 or −5, the patient is insufficiently aroused for delirium assessment. Researchers will repeat an independent assessment at the next predetermined point. If the RASS score is greater than −4, the CAM-ICU test will be performed. If RASS scores remain −4 or −5 beyond 1 hour after tracheal extubation, the patient will no longer receive the CAM-ICU test in the PACU, and the primary outcome will be recorded as missing data. Before discharge from PACU, EEG monitoring (5 minutes) and blood draw are conducted for participants.

In the hospital wards, participants are reassessed for delirium from postoperative days 1 to 3 in the morning and the afternoon. The visual analog scale is used to measure the level of pain at postoperative days 1 to 3. Participants complete measures of depression (9-item Patient Health Questionnaire),^30^ anxiety (7-item Generalized Anxiety Disorder Scale),^31^ and insomnia (Insomnia Severity Index)^32^ at postoperative day 3. Trained researchers conduct assessments blinded to the allocation.

